## Abstract

**Background:**

The common randomized controlled trial design has distinct limitations when applied to Chinese medicine, because Chinese medicine identifies and treats 'Chinese medicine patterns' rather than diagnosed diseases. Chinese medicine patterns are a group of associated symptoms, tongue appearances and pulse characteristics. These limitations could be overcome by developing new strategies to evaluate the effect of Chinese medicine. The idea behind pattern-based efficacy evaluations may optimize clinical trial design by identifying the responsiveness-related Chinese medicine patterns.

**Methods/Design:**

This is a two-stage multi-center trial of Chinese herbal medicine for the management of rheumatoid arthritis. The stage one trial is an open-label trial and aims to explore what groups of Chinese medicine information (such as symptoms) correlates with better efficacy, and the stage two trial is a randomized, controlled, double-blind, double-dummy clinical trial that incorporates the efficacy-related information identified in the stage-one trial into the inclusion criteria.

**Discussion:**

The indication of a Chinese herbal formula is a specific Chinese medicine pattern and not a single disease and stratifying a disease into several patterns with a group of symptoms is a feasible procedure in clinical trials. This study is the first to investigate whether this approach in the design of Chinese herbal medicine trials can improve responses.

**Trial registration:**

ChiCTR-TRC-10000989

## Background

Clinical trials are mainly aimed at showing the efficacy and safety of a therapy after initial indications are determined in preclinical studies, but the results obtained from a clinical trial have become less important in identifying the specific indications of a therapy. At present, "-omics"-based pharmacology contributes to individualized medicine, which attempts to find more specific indications for therapies by identifying biomarkers [1]. Similarly, Chinese medicine (CM) generally prescribes therapies based on the identification of CM patterns in the patient by analyzing the symptoms and characteristics [2].

All medicines should be rigorously tested [3,4], and the WHO Traditional Medicine Strategy suggests that clinical trials should be performed to establish the efficacy of CM [5]. Randomized clinical trials are useful to evaluate the efficacy of single drugs or combination therapy in a biomedical context [6]. However, they have distinct limitations when applied to CM because CM treatments focus on CM pattern classification [7]. Thus, alternative strategies, based on the CM concept, must be developed for the evaluation of CM efficacy and safety [8].

One important terminology in CM is "one formula based on one pattern", and the concept behind CM pattern-based individualized medication is to find out the responsiveness-related biocharacteristics for the interventions [9]. Thus, in CM practice, patients with rheumatoid arthritis (RA) can be treated with different therapies according their different patterns, which are a group of symptoms [10]. Therefore, the key factor in evaluating the efficacy of herbal therapy is to find out the specific CM pattern or indication for herbal therapy. Although CM pattern classification is complicated and difficult to understand in terms of making individualized herbal combinations for patients, CM patterns for specified herbal formulae could be identified by finding out the responsiveness-related CM information. Thus, it is reasonable to hypothesize that the CM pattern for one herbal therapy could be determined by comparing the differences of CM information between the responsive and non-responsive patients treated with the herbal therapy.

To test this hypothesis, we propose a two-stage clinical trial sponsored by the Institute of Basic Research in Clinical Medicine, China Academy of Chinese Medical Sciences in China. The primary objective of the trial was to find out the responsiveness-related CM symptoms that could be used as criteria for inclusion into secondary clinical trials. By comparing the difference in CM information between the responsive and non-responsive cases treated with one specific herbal intervention, the efficacy related information could be identified by statistical approaches. Secondary trials would then be aimed at evaluating the clinical efficacy for the herbal therapy by incorporating the efficacy related CM information into the inclusion criteria.

## Introduction to interventions

### CM interventions

The combination of Chinese herbal drugs Yi Shen Juan Bi (YSJB) and Tripterygium Wilfordii Polyglycoside (both drugs in tablet form) are approved as herbal medications by the State Food and Drug Administration (China) in patients with RA. Combination therapy is recommended by the Chinese Association of Integrative Medicine (unpublished data). The YSJB formula has been recognized as a valuable CM used in the treatment of RA. Clinically, YSJB has been shown to ameliorate symptoms and signs of RA and to decrease the erythrocyte sedimentation rate (ESR), C-reactive protein (CRP), and the rheumatic factor (RF) [11]. Additionally, the mechanisms underlying the efficacy of YSJB have been studied; YSJB significantly decreased the production of peritoneal macrophage-derived TNF-α, IL-1 and NO and significantly decreased prostaglandin E (PGE) and up-regulated Bax expression in rat synovium [12-14]. Components of YSJB are shown in Table 1. Tripterygium Wilfordii Polyglycoside (TWP, dark brown pills, patent number: Z34021048) is a commonly used anti-rheumatic herbal drug. In CM, extracts of Tripterygium wilfordii Hook F (TwHF, known as "lei gong teng" or "thunder god vine") are used to treat autoimmune and inflammatory conditions. Clinical trials suggest that TwHF may benefit patients with RA [15,16].

**Table 1 T1:** Components of Yi Shen Juan Bi (YSJB)

Chinese name	Latin name
Cang Er Zi	Fructus Xanthii
Congrong	Herba Cistanchis
Dang Gui	Radix angelica
Di Huang	Radix rehmanniae
Di Long	Pheretima
Gan Cao	Radix Glycyrrhizae
Gu Bus Ui	Rhizoma drynariae
Hu Zhang	Polygoni cuspidati
Ji Xue Teng	Caulis spatholobi
Jiang Can	Bombyx batryticatus
Lao Guan Cao	Herba erodii
Lu Xian Cao	Herba pyrolae
Qiang Lang Chong	Allomyrina dichotoma
Quan Xie	Scorpio
Shu Di Huang	Radix rehmanniae praeparata
Tu Bie Chong	Eupolyphaga seu steleophaga
Wu Gong	Scolopendra
Wu Shao She	Zaocys (stir-fried with wine)
Xu Chang Qing	Cynanchi paniculati
Xun Gu Feng	Herba Aristolochiae
Yan Hu Suo	Rhizoma corydalis
Yin Yang Huo	Herba epimedii
Zhi Feng Fang	Nidus vespae (stir-bakedg)
Zhi Feng Fang	Nidus Vespae

### Control interventions

The combination of methotrexate (MTX) and sulfasalazine (SSZ) is also a commonly used therapy for RA treatment [17], and the combination is used as a control in this clinical trial.

### Design

This is a two-stage, multi-center trial in the management of RA. The first-stage trial is an open-label trial and aims to explore which groups of CM-related symptoms correlates with better efficacy, and the second-stage trial is a 24-week randomized, controlled, double-blind, double-dummy clinical trial that incorporates the group of symptoms identified in the first-round trial in the inclusion criteria.

The hypotheses for the two-stage clinical trial to be tested are as follows:

1. The CM therapy is safe, acceptable and feasible, and at least 80% of the subjects will complete the CM therapy.

2. The specified group of participants treated with CM therapy will demonstrate significantly improved ACR20 responses compared to the positive control group.

A flow chart of the study design is shown in Figure 1.

**Figure 1 F1:**
[figure not shown]
**The flowchart of the two-stage trial design**.

## Stage one of the Trial

The first-stage trial is a 24-week open-label trial and is aimed at exploring what CM information correlates with better efficacy of the herbal intervention. The sample size is 120 cases.

### Inclusion criteria for participants

Eligible patients should be ≥ 18 and ≤ 70 years old and should have been diagnosed with RA according to American College of Rheumatology (ACR) classification criteria [18] and have active RA, which is defined as class I, II, or III RA, at the time of screening [19]. Patients are allowed to take stable doses of non-steroidal anti-inflammatory drugs or oral corticosteroids (≤10 mg prednisone or equivalent) ≥ 4 weeks before screening. Signed, informed consent from a patient or guardian will be required.

### Exclusion criteria for participants

Patients were excluded from the study if they received other commercial or experimental biological therapies for RA, were diagnosed with another inflammatory disease within one month of screening, or experienced uncontrolled or clinically significant systemic disease other than RA. Patients diagnosed with class IV RA as defined by ACR revised criteria for global functional status in RA or any major chronic inflammatory disease or connective tissue disease other than RA were also excluded. Patients would be ineligible if they had any laboratory abnormality that, in the opinion of the investigator, would prevent the patient from completing the study or interfere with the interpretation of the study results. Patients should not have received intra-articular or systemic corticosteroid injections or any investigational therapy within 4 weeks of screening, any disease-modifying anti-rheumatic drug other than MTX and SSZ within 4 weeks of screening, or cyclophosphamide within 4 weeks of the first dose of the investigational product. Patients would be ineligible if, in the investigator's opinion, they have any physical or psychiatric disorder that could interfere with their ability to give informed consent or participate in the study. Pregnant women would not be eligible for the study.

### Intervention

Tripterygium Wilfordii Polyglycoside tablets were provided by Jiangsu Meitong Co., Ltd (Z43020138). Tripterygium Wilfordii Polyglycoside or placebo were prescribed at 10 mg 3 times a day immediately after meals. Yi Shen Juan Bi (YSJB, dark brown pills, patent number: ZL200510040550) is prepared by Qingjiang Co., Ltd (Z10890004) and were prescribed at 1 pocket (8 g) 3 times a day immediately after meals.

### Outcome measures

The primary efficacy endpoint is the ACR20 response [20] at week 24. Secondary efficacy endpoints include the ACR50 and ACR70 responses and the individual components of the ACR. Patterns based on CM symptoms, joint function, the Disease Activity Score using the 28-joint count (DAS28), physical exam, laboratory tests, and patient-reported outcomes, including the Disability Index of the Health Assessment Questionnaire (HAQ) were also noted [21]. All of these endpoints over time in the study will be analyzed as exploratory endpoints. Safety endpoints include adverse events (AEs), serious AEs (SAEs), and laboratory abnormalities.

### Ethical considerations

The study was conducted according to the Declaration of Helsinki and the International Conference on Harmonization Tripartite Guideline on Good Clinical Practice [22]. Approvals from the appropriate research ethics committees were obtained at each participating study center. All patients were asked to provide written, informed consent before participating.

### Withdrawal criteria

Patients would be withdrawn from the study if the clinician found that they were in need of or were better served with another treatment or if the exclusion criteria were met. Patients would also be withdrawn from the study if according to the clinician's judgment clinical conditions worsened or if the patients withdrew their consent. The date and reason for discontinuation were noted. All patients who prematurely discontinue the trial would undergo a final evaluation.

### Recruitment

Patients were recruited through hospital advertisements, and patients with RA would be likely to receive Chinese herbal medicine therapies.

### Statistical analysis and primary results

Patients were analyzed according to the open-label study. The primary efficacy endpoint compared the ACR20 response rate at week 24. All secondary endpoints were pre-specified for sequential testing. The correlation between the CM symptoms and the response, T-tests and correlation analyses were used for the statistical analysis. For dichotomous variables, missing values were imputed using a non-responder imputation method, and for continuous variables, the primary analysis were based on observed cases. Our primary result shows that the patients with large amounts of clear urine, who spontaneous sweated and experienced night sweats were found to be positively correlated with the ACR 20 response. Further analysis shows that the ACR20 for the CM intervention is 76% if only the RA patients with the efficacy related CM symptoms could be treated with the CM intervention, though the ACR20 is 58% in all RA patients.

## Stage two of the Trial

The investigation will be a double-blind, double-dummy, controlled study in patients with active RA aimed at exploring the efficacy of the herbal intervention in RA patients with specific CM symptoms. The secondary stage will be designed by adding the efficacy related CM symptoms obtained from the stage-one trial as the inclusion criteria.

### Inclusion criteria for participants

To be enrolled, patients will have to meet the inclusion criteria of stage one and have to show the efficacy related CM symptoms from the first-stage trial. At moment, large amounts of clear urine, spontaneous sweated and experienced night sweats were found to be efficacy related symptoms, and should be included in the inclusion criteria. More analysis is still conducted and hopefully we could find more positive clinical manifestations for the inclusion criteria.

### Exclusion criteria for participants

The exclusion criteria will be approximately the same as those of stage one. RA patients without the efficacy related CM symptoms from the first-stage trial will be excluded. Also we are conducting further analysis and trying to find the CM symptoms which are negatively related to the ACR20 response, and the patients with the efficacy negatively related CM symptoms will be excluded.

### Sample size

This trial at stage 2 is designed as an active control superiority trial and intended to show superiority of CM intervention. The sample size calculation is based on the ACR20 response rate of the stage one of the trial. The primary results of the stage one trial (76% ACR20 response of CM intervention in the patients with the efficacy positively related CM symptoms) and our previous clinical data (53% ACR20 response in Western medicine intervention in the patients with the efficacy positively related CM symptoms). The sample size was established by comparing the rates of effectiveness between CM and Western medicine interventions (set α = 0.05, *β*= 0.10). Sample size could be 88 in both groups. With a dropout rate for follow-up as 20%, the sample size for each group could be 110 and 220 in the two groups.

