The ingredients in herbal products, with their relative, fixed-CM pattern feature, cannot be changed after the product is marketed. Thus, there is a dilemma in evaluating the efficacy of CM herbal products; the CM pattern is important for the evaluation, but it is difficult to understand. This two-stage clinical trial was designed to evaluate the efficacy of CM therapy (biomedical intervention could be included in terms of indication specification) based on the CM pattern identification concept, and the CM patterns could be identified by comparing the CM information between the responsive and non-responsive cases during the first-stage clinical trial.

YSJB and TWP are commonly used for the treatment of RA in CM, and the combination therapy with MTX and SSZ are also commonly used in biomedicine. In routine clinical trials, YSJB and TWP show less effective in RA treatment compared to biomedical intervention (unpublished data) because it is hard to incorporate CM pattern information in trials. The findings from the stage-one trial suggested that the group of patients with some CM symptoms have improved efficacy, and the stage-two clinical trial was designed by adding the group of symptoms selected in the first stage trial for inclusion criteria in the second trial. We hope that the ACR20 response can be improved in RA treatment with CM therapy due to the CM pattern classification concept utilized in the trial.

It is anticipated that this two-stage trial will take 24 months to complete. The first-stage trial is completed, and recruitment into the second-stage trial commenced in June 2010 with the first participant randomized in August 2010. The 24-week follow-up assessments will be completed in the end of 2011.

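### The 76% ACR20 rate behind the stage-two sample size is an uncorrected apparent rate from the data that selected the symptoms, so the stated 90% power rests on an optimistic input

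*Protocol article*

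**What the plan says.** Stage one is a 24-week open-label trial of 120 cases, with no control arm described. Its section on statistical analysis and primary results gives the method of symptom selection: "The correlation between the CM symptoms and the response, T-tests and correlation analyses were used for the statistical analysis". Three symptoms (large amounts of clear urine, spontaneous sweating, night sweats) "were found to be positively correlated with the ACR 20 response". The next sentence reports that "the ACR20 for the CM intervention is 76% if only the RA patients with the efficacy related CM symptoms could be treated" with it, "though the ACR20 is 58% in all RA patients".

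The stage-two Sample size section says that the calculation rests on the stage-one ACR20 rate. It enters "76% ACR20 response of CM intervention in the patients with the efficacy positively related CM symptoms" for CM and, from the authors' previous clinical data, "53% ACR20 response in Western medicine intervention in the patients with the efficacy positively related CM symptoms". With α = 0.05 and β = 0.10 it arrives at 88 per group, and at 110 per group (220 in total) for 20% dropout.

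The stage-two inclusion and exclusion criteria add that the search for further positively and negatively related symptoms continues. The stage-two analysis uses Fisher's exact test on all randomized patients, with missing responses counted as non-response.

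**The concern.** The symptoms were kept because patients who had them responded more often. The response rate was then read off in those same patients. Part of any apparent advantage in such a subgroup is chance that the selection step picked out, so the rate will on average be lower in new patients with the same symptoms. The article gives no hold-out sample, resampling, shrinkage, subgroup size or confidence interval for the 76%.

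The 23-point difference (76% minus 53%) is the only basis for the size of stage two and its 90% power. If the true CM rate in the selected population is lower, the trial has less power than stated. A null result could then be read as a failure of the pattern-based approach when the trial was too small for the real effect.

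**Working it through.** **Inputs.** CM rate 0.76, control rate 0.53, α = 0.05, power 0.90, 20% dropout (stage-two Sample size); 1:1 allocation (Randomization); Fisher's exact test (stage-two Statistical analysis); 120 stage-one patients and 58% ACR20 overall (stage one). The Sample size section does not give sidedness. Two-sided is taken because it reproduces the stated figure (one-sided gives 73 per arm).

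**1. The plan's own figure.** With p̄ = (0.76 + 0.53)/2 = 0.645:

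n = [1.960·√(2·0.645·0.355) + 1.282·√(0.76·0.24 + 0.53·0.47)]² / 0.23²
= [1.960·0.6767 + 1.282·0.6569]² / 0.0529
= 2.168² / 0.0529 ≈ 88.9 per arm.

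The arcsine formula gives 88.7. The stated 88 therefore reproduces to within rounding, and 88/0.8 = 110.

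**2. Power if the true CM rate is lower.** Exact two-sided Fisher power at 110 per arm, by full enumeration, control 53%:

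| True CM rate | Power |
|---|---|
| 76% | 93.5% |
| 75% | 91% |
| 74% | 88% |
| 72% | 79.5% |
| 70% | 69% |
| 67% (half of the 18-point gain lost) | 50% |
| 64% | 32% |
| 58% (no gain) | 9% |

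The midpoint is (58 + 76)/2 = 67. The table assumes that all 110 per arm are analysed and that 76% and 53% already count dropouts as non-responders.

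**3. Can selection alone give about 76%?** This is an illustration, not an estimate. Assumptions: 120 patients, true ACR20 58% whatever the symptoms, independent symptoms with prevalence 10–50%, and the best 3 of 10 to 60 candidates kept by correlation.

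- Patients with at least 2 of the 3 symptoms: mean apparent rate 71–81%; 28–72% of runs reach 76%.
- Patients with any of the 3: mean 63–68%; 1–8% of runs reach 76%.
- Patients with all 3: the apparent rate is higher still. In a companion run with 10–40 candidates and prevalence 30–50%, the mean was 71–88%.

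The documents do not say which of these rules defines the selected patients. The number of candidate symptoms and their prevalences are not given either.

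**4. Sampling error.** The size of the symptom-positive subgroup is not given. For assumed sizes of 25, 50 and 75, the Wilson 95% interval around 76% is about 57–89%, 63–86% and 65–84%, before any allowance for selection.

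**The case against.** **The design may still have 90% power.** If all 110 per arm are analysed with non-responder imputation, and the planning rates already include it, power at the stated rates is 93.5%. It is still 91% at a CM rate of 75%. This stands: about 1 point of bias is absorbed, so the 90% cannot be called false outright. The cushion depends on its condition, however. Stage one describes non-responder imputation, but the handling of dropouts behind the 53% is not stated. If both were completer rates with 20% dropout (0.8·76 = 60.8% against 0.8·53 = 42.4%), Fisher power is 74% with no selection bias at all.

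**The simulation rests on choices that the article does not make.** This also stands. With a latent correlation of 0.3 between symptoms, the case of 30 candidates and at least 2 of 3 falls from a mean of 78% (56% of runs reaching 76%) to 73% (35%). The simulation shows that selection could produce such a figure, not that it did.

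**Stage two is itself the independent test.** It is a separate randomized, double-blind comparison, so optimism in the 76% biases neither its effect estimate nor its type I error. That is right, and it limits the point to power.

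**Stronger readings that the documents do not support:**

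- A reader might infer that the 53% control rate contradicts the Discussion, which says "In routine clinical trials, YSJB and TWP show less effective in RA treatment compared to biomedical intervention". That statement gives no endpoint and no rate for either therapy, and it concerns routine trials, whereas the 53% is for symptom-positive patients. The 58% from open-label stage one cannot be carried into those trials as a floor for the control.
- A reader might infer that moving from open-label to double-blind must shrink the difference. The blinding of the data behind the 53% is not stated, so the effect on the 23 points is unknown.
- A reader might infer that a true benefit will probably be missed. By the table, that needs more than about half of the 18-point gain to be artefact, and nothing in the documents establishes this.

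**Conclusion.** The point holds as a weakness in the planning rate and in the power stated from it. The symptoms were selected on ACR20, and the 76% was then computed in the same stage-one data and used uncorrected, so it is too high in expectation. The size of the bias cannot be derived from the documents, so neither one corrected power nor one corrected sample size can be given.

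On the assumptions stated with the table, Fisher power falls below 90% once the true CM rate drops under about 75%, reaches 50% at 67%, and is 9% if the symptoms bring no gain over 58%. The sample-size arithmetic is correct. The validity of the stage-two comparison is not in question.

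**What to change.** 1. Repeat the whole symptom selection inside each bootstrap resample or cross-validation fold of the 120 stage-one patients, including the rule for how many symptoms a patient must have. Derive an optimism-corrected ACR20 rate for the selected group.
2. Use that rate as the planning value, and report the subgroup size and an interval with it.
3. Rewrite the stage-two Sample size section as the power of 110 per arm at the corrected rate and over CM rates from 58% to 76%. State whether both rates count dropouts as non-responders.
4. In the stage-one results, label the 76% as an uncorrected apparent rate.

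The cost is a small re-analysis of existing data and a rewritten paragraph. No extra patients are needed for this, although recruitment has already begun. The stated power will probably look less favourable: the fix does not raise power, but it makes a null result interpretable.

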### Randomization

Randomization will be controlled by an independent clinical research coordinator (CRC). First, the randomization form with the basic information of the participant who passed the screening phase will be transmitted by facsimile to the independent statistician. The randomization number in the randomization form will be left blank before arrival at the statistician. The statistician will then decide the randomization number based on the allocation sequence, which will be generated by a random number creation program in advance. The statistician will then return the randomization form filled in with the established number (specific ID number) to the CRC. The ratio of randomization allocation to the sites should be 1:1. The CRC will then inform the investigators of the specific ID number. The completion of this procedure will be guaranteed by the research organization.

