### Statistical analysis

Patients will be included for analysis according to the randomized treatment arm regardless of the actual treatment received during the study. All efficacy endpoints will be analyzed using the intent-to-treat analysis set, which will include all randomized patients regardless of whether they received an investigational product. The safety dataset will also include all patients who received ≥ 1 dose of an investigational product. The primary efficacy endpoint will be used to compare the ACR20 response rate at week 24 in the CM group with that of the biomedicine group. All secondary endpoints will be tested sequentially in a pre-specified order to control the one-error rate at 5% (two-sided). The comparisons of proportions (for dichotomous variables) among treatment arms will be performed using Fisher's exact test. For dichotomous variables, missing values will be imputed using a non-responder imputation method; for continuous variables, the primary analysis will be based on observed cases.

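### The stage-two size of 88 evaluable per group gives about 87% power, not 90%, under the Fisher's exact test that the plan names

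*Protocol article*

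**What the plan says.** The stage-two Sample size section of the protocol article describes a superiority comparison: "This trial at stage 2 is designed as an active control superiority trial". Its inputs are "76% ACR20 response of CM intervention in the patients with the efficacy positively related CM symptoms" and "53% ACR20 response in Western medicine intervention in the patients with the efficacy positively related CM symptoms", with "set α = 0.05" and beta 0.10. The result is "Sample size could be 88 in both groups", raised to 110 per group and 220 in total for 20% dropout. The section names neither a formula nor a test, and does not say whether alpha is one- or two-sided. The Randomization section gives the ratio: "The ratio of randomization allocation to the sites should be 1:1".

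The stage-two Statistical analysis section names the test: "The comparisons of proportions (for dichotomous variables) among treatment arms will be performed using Fisher's exact test". The primary endpoint, ACR20 response at week 24, is a proportion, so this is the primary test. The same section analyses all randomized patients by assigned arm, counts missing binary outcomes as non-response, and sets the sequential testing of secondary endpoints "to control the one-error rate at 5% (two-sided").

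**The concern.** Fisher's exact test is conservative: its actual type I error lies below the nominal level, and it therefore has less power than an uncorrected chi-square test at the same size. A sample size taken from a large-sample formula does not carry its power over to Fisher's test. Here the protocol fixes both the error rates and the test, and the two do not agree. At stake is whether the stated beta of 0.10 describes the comparison that will be made.

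**Working it through.** **Inputs.** p1 = 0.76, p2 = 0.53, alpha = 0.05, power = 0.90 and n = 88 per group (Sample size); 1:1 allocation (Randomization); Fisher's exact test, all randomized patients analysed, missing counted as non-response (Statistical analysis). Two-sided alpha is an inference, checked in step 1.

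**Step 1: reproduce 88.** Pooled normal formula, with mean rate (0.76 + 0.53)/2 = 0.645:

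n = [1.96 × √(2 × 0.645 × 0.355) + 1.2816 × √(0.76 × 0.24 + 0.53 × 0.47)]² / 0.23²

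= [1.326 + 0.842]² / 0.0529 = 4.701 / 0.0529 = 88.9.

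Rounded up this is 89; the arcsine formula gives 88.7. The stated 88 is within one patient. One-sided formulas give about 70 to 81, so 88 is reproduced only with a two-sided alpha. The dropout step is exact: 88 / (1 − 0.20) = 110.

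**Step 2: power under the planned test.** For each pair of responder counts (x, y), multiply the two binomial probabilities and sum over all tables where the test rejects at two-sided 0.05:

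power = Σ Bin(x; n, 0.76) × Bin(y; n, 0.53) × 1[p(x, y) ≤ 0.05].

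| n per group | Fisher's exact | Uncorrected chi-square |
|---|---|---|
| 88 | 86.7% | 89.9% |
| 89 | 87.2% | 90.2% |
| 97 | 89.9% | 92.4% |
| 98 | 90.2% | 92.5% |
| 110 | 93.5% | 95.2% |

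At 88 per group Fisher's test falls 90.0 − 86.7 = 3.3 points short. It reaches 90% at about 98, ten more evaluable patients per group.

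**Step 3: power for the analysis that will be run.** All 110 per group enter the primary comparison, so the answer depends on what 76% and 53% mean.

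- Both rates already count dropouts as non-responders: 76% v 53% at 110. Fisher 93.5%, chi-square 95.2%.
- Both are completer rates and 20% per group are imputed as non-responders: 0.80 × 76% = 60.8% and 0.80 × 53% = 42.4% at 110. Fisher 74.3%, chi-square 78.5%.

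In the second case the fall from 95.2% to 78.5% under the chi-square test comes from the diluted rates alone; using Fisher's test costs a further 4.2 points.

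**Step 4: type I error.** With 53% in both groups, the actual two-sided size at 110 per group is 3.6% for Fisher's test and 5.0% for the chi-square test. At 88 per group the chi-square size is 5.6%.

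**The case against.** The strongest answer is that 88 is not the number analysed. Intent-to-treat with non-responder imputation leaves no ACR20 outcome out, so the test is run on 110 per group. If the planning rates already count dropouts as non-responders, power is 93.5%, better than stated. This stands, and it limits the point to the figure given for 88. It does not remove the point: the stage-one analysis did use non-responder imputation, so the 76% may be on that basis, but nothing says so for the 53%, and adding 20% for dropout treats 88 as the number that carries the information.

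A reader might infer that the trial's true type II error is about 13%, that 220 patients are too few because of Fisher's test, or that 98 / 0.80, about 123 per group, must be randomized. The documents support none of these, because the plan does not analyse 88 per group. Where power at 110 is low, on the completer reading, imputation causes most of the loss. A reader might also take 88 for a miscalculation; it is a standard result, one patient below the rounded-up pooled figure.

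It can also be said that Fisher's test is a valid, deliberately conservative choice, and that sizing by a large-sample formula is common. Both are true. The choice may stay, but the power figure should then match it. Finally, two-sided alpha is not stated for the primary test. One-sided Fisher's test at 0.05 would give 92.4% at 88, but no one-sided formula tried yields 88, so the two-sided reading is much the likelier.

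**Conclusion.** The point holds as a mismatch between sizing method and planned test. On the plan's own inputs, and with two-sided alpha 0.05, 88 evaluable per group has about 87% power under Fisher's exact test, against the stated 90%. The shortfall is modest. On each of the three settings computed, the uncorrected chi-square gains about 2 to 4 points: 3.3 at 88, 1.7 at 110 with the rates unchanged, and 4.2 at 110 with diluted rates.

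The power of the 110-per-group analysis cannot be settled from the article. It is 93.5% or about 74% under Fisher's test on the two readings above, the second assuming 20% dropout in each group with every dropout imputed. A mixed basis, with dropouts counted in one rate only, would change the assumed difference itself. This open question matters more for power than the choice of test.

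**What to change.** Make the two sections agree in one of two ways.

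1. In Statistical analysis, name the uncorrected Pearson chi-square as the primary ACR20 test and keep Fisher's exact test as a sensitivity analysis. In Sample size, state 88 with 89.9% power, or 89. The cost is that type I error is no longer guaranteed at or below 5% (step 4). The change should be made before unblinding.
2. Keep Fisher's exact test and restate the power as about 87% at 88 evaluable per group.

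In either case, state in Sample size that alpha is two-sided, say whether 76% and 53% count dropouts as non-responders, and give the power of the 110-per-group intent-to-treat analysis on that basis. This takes a few sentences of text and no additional patients. If the rates prove to be completer rates, changing the test will not restore 90% (78.5% with chi-square), and the plan should report that power openly. A centre-stratified test is an option, but this point does not require it.
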